| **TITLE**: | **ASSESSMENT OF A THERAPEUTIC EDUCATION PROGRAM FOR PARKINSON’S DISEASE.**  **ETPARK Study** | |
| --- | --- | --- |
| **ORGANIZATION**: | Name,  Address, Telephone: | CHU TOULOUSE  Hôtel Dieu, [name]  [name] – France  Contact: [name]  [contact] |
| **STUDY PHYSICIAN**: | Name,  Address, Telephone: | [name]  Neurology Unit, Neuroscience Center,  CHU Toulouse  [contact]  E-mail: [contact] |
| **ASSOCIATE PHYSICIANS**: | Name,  Address: | [name], Neurology Unit,  Neuroscience Center, CHU Toulouse  [name], Neurology Unit,  Neuroscience Center, CHU Toulouse  [name], Neurology Unit,  Neuroscience Center, CHU Toulouse  [name], Neuroscience Center Coordinator, CHU Toulouse  [contact] |
| **OTHER PARTICIPANTS:** | Name,  Address: | [name] (logistics and methodological support)  Clinical Investigation Center, CHU Toulouse  [contact]  [name] TAP- biostatistician,  Clinical Investigation Center, CHU Toulouse  [name], IDE,  Neuroscience Center, CHU Toulouse  [name] (Medical Information Department at CHU Toulouse)  [name] (CPAM) |
| **TYPE OF STUDY**: | *Open, randomized study* | |
| **DURATION OF THE PROJECT**: | 3 years | |
| **NUMBER OF SUBJECTS**: | 120 patients | |
| **PUBLIC HEALTH LAW** of 9 August 2004 | YES, research aimed at assessing intermediate care. | |
| **Registration No.**: | 2008-A00720-55 | |
| **KEYWORDS**: | Parkinson’s, therapeutic education, quality of life, medico-economic study. | |

1. ABSTRACT

**CONTEXT OF THE RESEARCH PROJECT:**

Antiparkinsonian treatments are only symptomatic and are often insufficient, especially when the disease is progressive. A therapeutic education program (TEP) accompanying the usual medical antiparkinsonian treatment could have a beneficial action on the various components of the disease and thus improve the Parkinson’s patient’s quality of life.

A few publications currently exist that talk about the interest of therapeutic education in Parkinson’s disease, reporting an improvement in certain aspects of quality of life, psychological condition and treatment compliance among Parkinson’s patients. As far as we know, no study of this kind has been carried out in France.

**OBJECTIVES OF THE RESEARCH PROJECT**:

The main objective of the study is to demonstrate the improvement in quality of life among Parkinson’s patients who benefit from a TEP program compared with Parkinson’s patients who do not benefit from such a program. The secondary objectives of the study are to compare the motor condition, psychological condition, social adjustment and medical costs in the two groups of Parkinson’s patients.

**METHODS AND TOOLS:**

The study is an open, randomized, monocentric, comparative prospective study of 2 groups of Parkinson’s patients (the first following a TEP program for 12 months, the second not following this program). We will assess the quality of life of Parkinson’s patients using a specific scale (PDQ-39) and a general scale (SF-36) at 6 and 12 months in 120 Parkinson’s patients (60 in each group). We will also assess the motor condition, psychological condition and social adjustment of the two patient groups. We will gather figures on medical costs using a healthcare consumption notebook indicating the drugs taken, hospitalizations, consultations, etc.

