### Main criterion

**Self-assessment questionnaire on quality of life specific to Parkinson’s disease**

Quality of life will be assessed using a specific scale (PDQ-39).

We will use the specific self-assessment measurement questionnaire, PDQ-39 (Parkinson's Disease Quality of Life) (De Boer et al., 1996). Its specific indicators are suited to detecting observable variations in the quality of life for a given disease, and in principle cannot be used to make comparisons between care programs that address different diseases (Carrere, 1997). The PDQ-39 is made up of 39 health-related questions that are to be answered retrospectively over a period of 1 month using 5 levels of frequency (always, often, sometimes, rarely, never). This specific quality of life measurement instrument assesses 8 dimensions of Parkinson’s patients’ health: mobility, everyday activities, emotional well-being, psychological stress, social support, cognitive disorders, communication and physical discomfort.

- 1. Secondary criteria

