### Exclusion criteria

The patient will not be included for the following reasons:

- Patient with an atypical non-idiopathic Parkinsonian syndrome (such as Progressive Supranuclear Palsy (PSP), Multiple System Atrophy (MSA), Corticobasal Degeneration (CBD), etc.);
- Patients with a Parkinsonian syndrome induced by a drug;
- Patient already included in a clinical trial at the time of the study;
- Patient at a Hoehn and Yahr stage of 5;
- Patient with a severe or progressive psychiatric illness or dopaminergic psychosis currently considered as being progressive;
- Patient having undergone deep brain stimulation within the last 3 months or planning to have one during the year;
- Patient incapable of understanding the protocol, filling in a notebook or any other assessment criterion or of following the clinical trial procedures;
- Patient with cognitive decline that could interfere with the assessment;
- Patient under temporary guardianship/full guardianship/judicial protection.
  1. Number of subjects required

If we want a power of 80% for a difference of 4 points in quality of life (PDQ-39), given a standard deviation of 17 points and a level of 5% in a one-tailed test, we must recruit 111 Parkinson’s patients given a correlation coefficient of 50% between the answers for the two periods. Given the potential withdrawals from the trials, we will recruit 120 patients.

The number of subjects was calculated using data from a study using the PDQ-39 quality of life scale on Parkinson’s patients (Brefel-Courbon et al., 2003).

- 1. Recruitment methods

Patients with Parkinson’s disease will be selected at the Neurology consultation services at the 2 hospitals in Toulouse (Purpan and Rangueil) by neurologists specialized in caring for Parkinson’s patients ([name], [name], [name], [name]) or at the movement disorder unit of the Neurology service at Purpan Hospital. This study seeks to be pragmatic, so we will propose this study consecutively and not selectively to all Parkinson’s patients meeting the inclusion and exclusion criteria.

We expect an average recruitment of 5 to 10 patients a month. The duration of inclusion should be 24 months.

- 1. Randomization

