### Follow-up and end-of-study visits

Patients will be assessed during a normal neurology follow-up consultation at 6 and 12 months after their inclusion.

During these 2 visits, the patient:

- will receive a neurological examination with a motor rating;
- fill in the self-assessment questionnaires;
- return the completed notebook and receive the notebook for the next visit (for the visit at 6 months).
  1. Data analysis

Data will be saved using the SAS software. The data input form will correspond exactly to the paper form used for gathering data.

The data will be made anonymous before its collation.

The statistical analysis will be descriptive as well as inferential:

- Qualitative variables will be described by presenting the frequency of each modality of these variables. Quantitative variables will be analyzed to establish the median, mean, standard deviation and extreme values.

- Quality of life will be analyzed classically using a linear model including a fixed treatment effect.

Comparisons of the medical costs, motor and psychological symptomatology (secondary quantitative assessment criteria) between two treatments will also be carried out in accordance with the process described above.

1. Expected consequences of the results of the project

If the impact of a TEP program is positive in terms of quality of life and if it does not produce additional costs, this type of care will be generalized for Parkinson’s disease and will give rise to contributions at national and international conferences.

1. Provisional schedule

Start of inclusions September 2008

End of inclusions September 2010

End of patient follow-up September 2011

Analysis of the results December 2011

1. Regulatory and ethical aspects

In accordance with law No. 2004-806 of 9 August 2004 relative to public health policy and its implementing orders, the project comes within the framework of an assessment of intermediate care and the study is subject to the opinion of a CPP (Comité de Protection des Personnes Sud-ouest et Outre-Mer – Institutional Review Board of the Southwest and Overseas Possessions). The research will not be implemented until a favorable opinion is received from the CPP.

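### The trial is sized for a single one-tailed 5% test of the PDQ-39, but the protocol does not say which PDQ-39 score, or which follow-up visit, decides the main objective

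*Protocol*

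**What the plan says.** - **Main criterion.** This section names the PDQ-39 and describes the questionnaire: 39 items, five frequency levels, one-month recall. It adds that "This specific quality of life measurement instrument assesses 8 dimensions" and lists them. It names no summary score, no decisive dimension and no time point.
- **Timing.** The abstract (Methods and tools) refers to assessment "using a specific scale (PDQ-39) and a general scale (SF-36) at 6 and 12 months". The section on follow-up and end-of-study visits confirms: "Patients will be assessed during a normal neurology follow-up consultation at 6 and 12 months after their inclusion". Questionnaires are also completed at the inclusion visit, so each patient has up to three PDQ-39 assessments. Neither follow-up visit is called primary.
- **Data analysis.** "Quality of life will be analyzed classically using a linear model including a fixed treatment effect". The sentence gives no score and no visit.
- **Number of subjects required.** The calculation uses 80% power, a 4-point PDQ-39 difference, a standard deviation of 17, "a level of 5% in a one-tailed test", and a correlation of 50% between two periods that are not identified. It arrives at 111 patients, raised to 120 for withdrawals. The error level is stated only here.

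**The concern.** A primary endpoint needs an instrument, a score and a time point. Here only the instrument is fixed. The sizing paragraph speaks as if there were one PDQ-39 number compared once, while the collection schedule yields two post-baseline occasions and the questionnaire yields several scores.

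If the choice remains open when the data are seen, or if both visits are tested and either may carry the claim, the chance of a false positive on the main objective exceeds 5%. The design makes this matter more: the trial is open, the outcome is self-reported, and the level is already one-tailed. The section on expected consequences says that a favourable quality-of-life result without extra cost would lead to this type of care being generalised. The result that triggers such a step should be one identified in advance.

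**Working it through.** **Inputs from the protocol:** difference 4, SD 17, correlation 0.5, one-tailed alpha 0.05, power 0.80 (Number of subjects required); follow-up at 6 and 12 months (abstract and visit sections).

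**Step 1. Reproduce the plan's figure.** The stated number matches a single paired comparison:
- SD of change = 17 × √(2 × (1 − 0.5)) = 17
- n = (17 × (1.645 + 0.842) / 4)² = 111.7, against 111 stated

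This is one test at one-tailed 5% with no allowance for a second. The formula is a within-patient one, whereas the objective compares two groups. That is a separate question; the formula is used here only to show how many tests the sizing assumed.

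**Step 2. Look for that one test in the rest of the protocol.**

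| Element | Sizing paragraph | Main criterion, visits, analysis |
| --- | --- | --- |
| Score | one PDQ-39 quantity | instrument only |
| Visit | two unnamed periods | months 6 and 12, neither primary |
| Level | one-tailed 5% | not stated |

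With three assessments, the two periods could be baseline and month 6, baseline and month 12, or months 6 and 12. The sizing paragraph therefore does not identify the decisive visit either.

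**Step 3. Error rate if either visit could count.** Assume one score, a one-tailed 5% test at each visit, and success if at least one is significant. With no true effect and correlation r between the two test statistics:

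P(at least one) = 0.05 + 0.05 − P(both exceed 1.645)

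| r (assumed) | P(both) | P(at least one) |
| --- | --- | --- |
| 0.3 | 0.0071 | 9.3% |
| 0.5 | 0.0122 | 8.8% |
| 0.7 | 0.0196 | 8.0% |

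Independence would give 1 − 0.95² = 9.75%. The central value borrows the protocol's 0.5, but since the protocol does not say which two periods that figure joins, it is an assumption here. If both comparisons were adjusted for baseline and all three assessments correlated at 0.5, the relevant r would be (0.5 − 0.25) / (1 − 0.25) = 0.33, which is inside the range shown.

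**Step 4. Cost of keeping both visits as routes to success.** Splitting the level gives 0.05 / 2 = 0.025 per visit. The protocol's own formula then needs (17 × (1.960 + 0.842) / 4)² = 141.8, or 142 patients instead of 111. Naming one visit avoids this.

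**The case against.** The strongest reply is that the protocol does not describe multiple testing. The only place that states an error level attaches it to one 4-point difference, and 111 reproduces as one test. The eight dimensions appear in a description of the questionnaire, and the two visits appear as a collection schedule. Model terms and multiplicity rules are commonly left to a statistical analysis plan, which may exist and is not shown.

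Much of this stands, and it rules out two stronger readings.

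- **Sixteen tests.** A reader might infer that eight dimensions at two visits are each tested at one-tailed 5%, with any success counting, so that the plan fails to deliver 5%. No section says so. Error rates computed on that basis describe a plan the protocol does not contain.
- **Pooled visits.** A reader might infer that both visits enter the linear model as if they were independent observations. The sentence says the model includes a treatment effect. It does not say that this is the only term or that the visits are pooled, and the sizing paragraph shows that within-patient correlation was considered.

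The reply does not remove the gap. The score and time point of the primary endpoint define the main objective and belong in the protocol. The section written to fix the endpoint leaves both open, which goes beyond routine analysis detail. Whether an analysis plan later closed the gap cannot be known from this document.

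**Conclusion.** The point holds as a badly fixed primary endpoint. The protocol commits to one one-tailed 5% test without saying which score at which visit it applies to. Inflation of the error rate is possible but not demonstrated, because the protocol states no rule under which either visit would suffice.

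The size is therefore conditional: about 8.8% instead of 5% if either follow-up visit on one score could support the main objective, with a range of 8.0% to 9.3%. It rests on an assumed between-visit correlation of 0.7 to 0.3, two unadjusted one-tailed tests, and an either-visit rule. Allowing single dimensions to count as well would raise it further, but no figure is put on that because the text gives no basis for such a rule. With one named score at one named visit, the level is 5%. The change should be made, since it determines what the trial can conclude.

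**What to change.** In the main-criterion and data-analysis sections, name one primary comparison. A suitable choice is the between-group difference in one overall PDQ-39 score, with its scoring rule stated, at month 12, from a linear model adjusted for the baseline PDQ-39 already collected. Month 12 is my inference from the 12-month length of the programme; the protocol does not designate it, and the sponsor should confirm it.

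Make month 6 and the eight dimension scores secondary, reported with confidence intervals and without a claim on the main objective. If both visits are modelled together, account for within-patient correlation and state which visit's contrast is primary. In the sample-size paragraph, say which score and which two assessments the 4 points and the correlation refer to.

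The cost is a few words and no extra data. The downside is that an effect seen only at month 6, or only in one dimension, can no longer count as success. If the sponsor wants both visits to remain routes to success, a multiplicity rule and a new sample-size calculation are needed.

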**CONDUCT AND DURATION OF THE PROJECT**:

Within each group, the various parameters will be gathered at the baseline and then at 6 and 12 months during a normal neurology follow-up consultation. The TEP program will include an initial consultation, then individual follow-up consultations (1 to 3 per three-month period), thematic group sessions (2 or 3 per six-month period), and then an assessment consultation at the end of the 12-month period. The inclusion period will last 24 months and the total duration of the study will be 36 months.

**IMPACT OF THE EXPECTED RESULTS:**

The results expected are an improvement in the quality of life among the Parkinson’s patients who follow a TEP program compared with the Parkinson’s patients who do not follow such a program.

We hypothesize that there will be a cost differential in favor of the Parkinson’s patients who follow a TEP program.

1. SCIENTIFIC JUSTIFICATION AND GENERAL DESCRIPTION

Parkinson’s disease, with a prevalence of 150/100,000 inhabitants, is the second leading cause of neurodegenerative disorders, behind Alzheimer’s disease (Petit et al., 1994). It concerns approximately 2/3 to 3/4 of all Parkinsonian syndromes and affects approximately 1.5% of all subject over the age of 60 (Tison, 1998). A chronic, degenerative neurological disease, it is characterized not only by a motor symptomatology (akinesia, stiffness, rest tremor, postural anomalies) but also cognitive and psychological disorders, sleep disturbances, pain and sexual dysfunction (Fitzsimmons et al., 1993). This varied symptomatology can therefore affect certain aspects of everyday life. Several studies have shown that there is an alteration of the quality of life with Parkinson’s disease (Karlsen et al., 1999; Schrag et al., 2000; Riazi et al., 2003). Antiparkinsonian treatments are only symptomatic and often insufficient, especially when the disease is progressive. Nearly half of all Parkinson’s patients use at least one alternative therapy (Rajendran et al., 2001).

A therapeutic education program, alongside the usual antiparkinsonian treatment, could have a beneficial action on the various components of the disease and thus improve the quality of life of Parkinson’s patients.

A few publications currently exist that talk about the interest of therapeutic education in Parkinson’s disease (Simons et al., 2006; Shimbo et al., 2004; Montgomery et al., 1994; Mercer et al., 1996; Macht et al., 2007, Grosser et al., 2007). But many of them do not assess therapeutic education with a sufficient methodology (Simons et al., 2006; Shimbo et al., 2004; Macht et al., 2007). Indeed, these studies do not include a control group and only demonstrate feasibility and the satisfaction felt by the patients and their caregivers. Three randomized comparative studies carried out in the United States and the United Kingdom reported an improvement in certain aspects of quality of life, psychological condition and treatment compliance in Parkinson’s patients (Montgomery et al., 1994; Mercer et al., 1996; Grosser et al., 2007). As far as we know, no study of this kind has been carried out in France.

In France, we can nonetheless take inspiration from the experience acquired by diabetologists concerning the interest of therapeutic education in treating diabetes. In 2002, the ANAES (Agence nationale d'accréditation et d'évaluation en santé – National Healthcare Accreditation and Assessment Agency) validated therapeutic education as a necessary, integral part of care for diabetic patients. Diabetes, like Parkinson’s disease, is a chronic disease in which intervention by the patient is by no means insignificant.

Parkinson’s disease in everyday life requires the people affected (and/or their caregivers):

- to take part personally in the decisions that will influence the effectiveness of their treatment (diet, physical activity, body maintenance and control, self-monitoring of symptoms, personal health practices, adequate specialized medical and paramedical appointments, etc.);
- and to ensure prevention or early screening for possible complications, notably iatrogenic effects.

Since 2005, our experiment at the abnormal movement unit of the CHU Toulouse University Hospital Center has shown that weekly meetings with hospitalized patients suffering from Parkinson’s disease, whether accompanied by their spouse or not, under the responsibility of a nurse and a physician aware of the interest of therapeutic education, enables patients to integrate the principles behind their treatment, the therapeutic outlook for the future, and the prognosis for their disease. This pilot experiment leads to a better acceptance of their disease, better treatment compliance and easier relations with caregivers and physicians.

Lastly, the current economic context makes it necessary to assess the cost of this kind of care. It is possible that an improvement in the quality of life and a better management of care for their chronic disease may lead to a reduction in healthcare consumption.

It is therefore important to undertake a medico-economic study in order to determine the impact of a therapeutic education program in Parkinson’s disease.

**Therapeutic education for patients (TEP)**

According to the WHO (1996), therapeutic education for patients aims at helping patients to acquire or maintain the skills they need to manage their life with a chronic disease as well as possible. This is a permanent, integral part of the patient’s care. It includes organized activities, including psychosocial support designed to keep patients’ aware and informed of their disease, their care, hospital procedures and organization and the behaviors related to healthcare and the disease. The goal is to help them (as well as their families) to understand their disease and their treatment, to work together and shoulder their responsibilities in their own care with a view to helping them to maintain and improve their quality of life.

The purposes of TEP include:

- the patient’s acquisition and maintenance of self-care skills (adapting drug doses to the motor condition, performing technical healthcare gestures, undertaking a program of physical activity, etc.);

- acquisition of psychosocial adjustment skills (knowing how to manage one’s emotions and managing one’s stress toward Parkinson’s disease, etc.).

TEP is therefore designed for all Parkinson’s patients, no matter what the stage of their disease, and for the people around them:

- because it is complementary and inseparable from their treatment and care, relieving their symptoms and preventing complications.

- because it contributes to improving patients’ health condition (biological and clinical) and their quality of life as well as that of those around them.

This TEP program is drawn up with the patient and personalized for his/her needs (personal or therapeutic). It facilitates or organizes interventions by other healthcare professionals such as psychologists, physiotherapists, social workers, dieticians, occupational therapists, etc.

This TEP program is undertaken:

- after announcing the diagnosis, to help understand, reformulate and provide psychological support;
- during the patient’s regular follow-up consultation, to consolidate skills, make updates for better compliance, good management of side effects and optimize quality of life;
- during an in-depth follow-up consultation, in a difficult period, if a patient is having difficulties with learning.

There are four steps:

- the educational diagnosis, focusing on the patient’s needs (what they have, what they do, what they know, what they think, who they are, what projects they have);
- skills to be acquired, objectives for the patient to reach, therapeutic objectives, contract;
- the educational methods, pedagogical tools (program of consultations, participation in group sessions);
- regular assessment of the progress made: what the patients know, what they know how to do, what they understand, what remains to be learnt, have they made progress in their project.

We therefore want to set up a medico-economic study aimed at assessing the impact of a therapeutic education program on patients afflicted with Parkinson’s disease.

